**Methods and analysis:**

We will test the hypothesis that AI-supported DR screening increases the proportion of persons with true referable DR who attend the central ophthalmology clinic following referral after screening in a single-masked, parallel group, individually randomised controlled trial. Participants (2364) will be randomised (1:1 ratio) to either AI-supported or the standard of care DR screening pathway. Participants allocated to the AI-supported screening pathway will receive their result followed by point-of-screening counselling immediately after retinal image capture. Participants in the standard of care arm will receive their result and counselling by phone once the retinal images have been graded in the usual way (typically after 2–4 weeks). The primary outcome is the proportion of persons with true referable DR attending the central ophthalmology clinic within 8 weeks of screening. Secondary outcomes, by trial arm, include the proportion of persons attending the central ophthalmology clinic out of all those referred, sensitivity and specificity, number of false positive referrals, acceptability and fidelity of AI-supported screening.

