### Follow-up assessment

All participants screened in the trial will be tracked to determine whether or not they attend the central ophthalmology clinic. Any participant recommended to attend a follow-up appointment who has not done so within 8 weeks of screening will be considered a non-attender. A follow-up period of less than 8 weeks could bias in favour of the intervention as some participants in the standard of care arm may not receive their screening result until 3–4 weeks after screening. As attendance at the central ophthalmology clinic beyond 8 weeks becomes increasingly less attributable to the DR screening result, it is our view that attendance within 8 weeks of screening is most appropriate.

For participants who attend the ophthalmology clinic we will document what, if any, treatment they are recommended and whether they commence the recommended treatment.

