Time to presentation at hospital	The time to presentation at hospital will be compared between trial arms for all those referred to the central ophthalmology clinic after screening. We will use Cox proportional hazards regression with trial arm as the primary predictor. Survival curves using Kaplan-Meier will be plotted for both trial arms to represent the time to presentation at hospital.
Incremental cost per QALY gained	The economic evaluation aims to assess the cost-effectiveness of an AI-supported screening model compared with standard of care model. Cost-effectiveness results will be expressed in terms of incremental cost-effectiveness ratios (ICERs) per QALY gained. A Markov model will be built to undertake the analysis. Both deterministic and probabilistic sensitivity analyses will be performed to test the robustness of the model. Uncertainty in the parameters in the model will be reflected using probability distributions and the overall decision uncertainty will be presented using cost-effectiveness acceptability curves.
Acceptability, appropriateness and fidelity of AI screening	A process evaluation will be embedded within the trial and will be undertaken using the Medical Research Council guidance.^24^ Using semistructured interviews with participants, screening team staff, ophthalmologists and Ministry of Health officials we will assess the acceptability of AI-supported DR screening from different perspectives (patients, staff, policy makers). These qualitative data will be analysed using NVivo according to a condensation of meaning analysis and units of meaning will be coded into central themes. The fidelity of AI-supported screening will be assessed during the trial by random spot checks evaluating the delivery of the intervention. Staff members will be asked to keep a log of any difficulties encountered while delivering the intervention, thereby highlighting implementation barriers and challenges.

AI, artificial intelligence; DR, diabetic retinopathy; QALY, quality-adjusted life year.

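### Time to presentation is summarised by a single Cox hazard ratio, although the standard arm gets its result about 2–4 weeks later by design, so that ratio mixes the delay with final attendance and shifts with the follow-up horizon

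*Protocol article*

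**What the plan says.** In Table 3 (Secondary outcome analysis), the row for time to presentation sets the comparison: "The time to presentation at hospital will be compared between trial arms for all those referred to the central ophthalmology clinic after screening". The effect measure follows: "We will use Cox proportional hazards regression with trial arm as the primary predictor". A display is added: "Survival curves using Kaplan-Meier will be plotted for both trial arms to represent the time to presentation at hospital". The row gives no time origin, no censoring time and no other between-arm summary.

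The timing of results differs by design. In the Abstract, AI-arm participants "will receive their result followed by point-of-screening counselling immediately after retinal image capture". The standard arm gets its result by phone "once the retinal images have been graded in the usual way (typically after 2–4 weeks"). The Masking section confirms that the standard arm has no feedback at screening. The Follow-up assessment section recognises the consequence for the binary outcome: "some participants in the standard of care arm may not receive their screening result until 3–4 weeks after screening", and it rejects a window shorter than 8 weeks because that could favour the intervention.

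**The concern.** A Cox model with arm as its only term reports one number, which describes the arms fully only if the ratio of their attendance rates is constant over time. Here one arm can act on a result from day 0, and most of the other has nothing to act on for weeks. People already attending the clinic are excluded (Table 1), so attendance before a result should be low. The change in the ratio over time is therefore known before any data are collected.

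What is at stake is interpretation. A reader of a published hazard ratio would take it as a sustained higher rate of attendance in the AI arm. The same value can arise from a pure head start with almost no difference in who has attended by 8 weeks, or from a real gap in attendance.

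**Working it through.** **Inputs from the protocol.** Result at day 0 (AI arm) or typically 2–4 weeks (standard arm); attendance window of 8 weeks from screening; planning values of 42% and 56% attendance (Sample size considerations). The planning values refer to people with true referable DR, while this outcome covers all referred, so they serve here as an illustration.

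**The plan's own figure.** No figure is given for time to presentation. The planning values do reproduce. With two-sided 5% (assumed from the 95% CI) and 90% power, n = [1.96·√(2·0.49·0.51) + 1.2816·√(0.42·0.58 + 0.56·0.44)]² / 0.14² = (1.386 + 0.897)² / 0.0196 ≈ 266 per arm, and 1182 × 0.225 = 265.95.

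**Assumptions added.** Time runs from screening. The standard-arm delay D is uniform on 2–4 weeks. Attendance before a result is 0, 10% or 25% of the AI-arm hazard. The Cox ratio exp(β) solves Σ over events of [x − n₁e^β/(n₁e^β + n₀)] = 0, where x is 1 for the AI arm and n₁, n₀ are the numbers at risk. It was computed on simulated arms of 100,000 or 200,000.

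**Pattern A: constant hazards after the result, 42% vs 56% at 8 weeks.**
- AI-arm hazard: −ln(0.44)/8 = 0.1026 per week.
- Standard-arm hazard h after the result, with no earlier attendance, solves (e^(−4h) − e^(−6h))/(2h) = 0.58, so h = 0.1093.
- Once all results are out, the ratio is 0.1026/0.1093 = 0.94.

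| Pre-result attendance | HR wk 0–2 | wk 2–4 | wk 4–8 | Cox HR censored at 4 / 6 / 8 / 12 / 26 wk |
|---|---|---|---|---|
| none | infinite | 1.96 | 0.94 | 4.07 / 2.11 / 1.72 / 1.46 / 1.29 |
| 10% | 10.15 | 1.89 | 0.97 | 3.29 / 1.98 / 1.67 / 1.46 / 1.30 |
| 25% | 3.97 | 1.76 | 1.10 | 2.49 / 1.83 / 1.64 / 1.48 / 1.36 |

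With 42% in both arms at 8 weeks and no pre-result attendance, the Cox ratio is 2.62 at 4 weeks, 1.11 at 8 and 0.82 at 26, so its direction changes with the horizon.

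**Pattern B: the same 56% eventually attend in both arms**, with exponential time from result to visit.
- Mean 2 weeks: interval ratios are infinite, 1.03, 0.29 and 0.25 in weeks 0–2, 2–4, 4–6 and 6–8. The Cox ratio is 1.47, 1.37 and 1.35 at 8, 12 and 26 weeks.
- Mean 4 weeks: the Cox ratio is 1.54, 1.32 and 1.23.
- Mean 1 week: attendance by 8 weeks is 56.1% vs 55.6%, yet the Cox ratio at 8 weeks is 1.48.

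**The mixing at a fixed 8-week horizon.** The last case has an attendance gap of 56.1 − 55.6 = 0.5 percentage points and a ratio of 1.48. A case with equal post-result hazards and 25% pre-result attendance has 56.1% vs 44.6%, a gap of 11.5 points, and a ratio of 1.51. The two ratios are almost the same.

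**The alternative measure in pattern B.** Restricted mean time over 8 weeks is the area under the not-yet-attended curve. For mean 2 weeks:
- AI arm: 8 − 0.56·[8 − 2(1 − e^(−4))] = 4.62 weeks.
- Standard arm: the average of e^(−(8−D)/2) is e^(−2) − e^(−3) = 0.0856, so 8 − 0.56·[5 − 2(1 − 0.0856)] = 6.22 weeks.
- Difference: 1.60 weeks, with attendance by 8 weeks of 0.56·(1 − e^(−4)) = 55.0% vs 0.56·(1 − 0.0856) = 51.2%.

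Read together, these two figures separate speed from final attendance.

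**The case against.** Several objections have force.

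- **Time origin.** The row does not state it. If time ran from receipt of the result, the built-in delay would vanish. The attendance window runs from screening, however, and starting at the result would discard the benefit of an immediate one. Screening is the likelier origin, but it is inferred.
- **A crossing of the hazards.** A reader might infer that the late ratio must fall well below 1. The documents do not support that. It follows from assuming a fixed share of eventual attenders (pattern B); with constant hazards at the planning values it is 0.94 to 1.10.
- **Horizon.** The Follow-up assessment section counts anyone not seen by 8 weeks as a non-attender, and nothing plans censoring at 12 or 26 weeks. If the 8-week rule carries over, dependence on the horizon matters less. The mixing of delay and attendance at 8 weeks remains.
- **Direction.** In the equal-attendance scenarios the AI arm does present sooner, so a ratio above 1 at 8 weeks points the right way. A test of identical curves also remains valid.
- **Other planned output.** The Kaplan-Meier curves and the two 8-week attendance proportions would let a careful reader separate speed from attendance.
- **An unseen SAP.** Proportionality checks are commonly left to it. A check would only confirm a delay that the design already guarantees; the effect measure is what the protocol fixes.

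**Conclusion.** The point holds in limited form. With time from screening, a single hazard ratio is a poor summary of this secondary outcome, because the rate ratio changes by design from very large (about 4 even with 25% pre-result attendance) to near or below 1. At 8 weeks the Cox ratio is about 1.5 with equal eventual attendance and 1.64 to 1.72 at the planning values. These sizes rest on the assumed delay and visit-timing patterns; the early excess rests only on the stated result timing and low attendance before a result.

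Stronger readings go too far. The documents do not show that hazards cannot be proportional under any origin: 2–4 weeks is called typical, and some may attend earlier. Nor is the ratio meaningless: at a stated horizon it is an estimable average. That AI output selects the referred group in one arm and residents' grading in the other is a separate question, and this point does not require a change of denominator. The primary 8-week logistic analysis is untouched.

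**What to change.** In the time-to-presentation row of Table 3:

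- State screening as the time origin and 8 weeks as the censoring time.
- Make the between-arm difference in restricted mean time to presentation over 8 weeks, with its 95% CI, the effect measure. It also depends on the horizon, but the horizon is then explicit and the unit is weeks.
- Add Kaplan-Meier attendance differences at set weeks, such as 4 and 8.
- Keep the Kaplan-Meier plot.
- Report any Cox hazard ratio only as supplementary, labelled as a time average to 8 weeks or split by period.

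The cost is one table row, a few more lines of analysis and a less familiar summary. No new data are needed, and neither the sample size nor the primary analysis changes.

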#### Interim analysis

As there is negligible risk to participants an interim analysis is not required and data analysis will take place at the end of the study.

All retinal images collected during the study will be graded by local Tanzanian ophthalmology residents. Any images that are graded as referable DR by the Tanzanian graders but were graded as non-referable by the AI (potential false negatives) will be reviewed by a senior grader. If the senior grader concludes that the participant does meet the referral threshold, participants will be contacted and advised to attend the eye clinic, thereby ensuring minimal risk to patients.

In such circumstances, the initial result from the AI grading will be used in the analysis and would therefore not affect the results.

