### Outcome measures

#### Primary outcome measure

The primary outcome will be the proportion of persons with true referable DR who attend the central ophthalmology clinic within 8 weeks of screening out of all those with true referable DR (defined by the reference standard), by trial arm.

All retinal images will be graded by UK-certified graders to provide the reference standard. It will be these gradings that will determine which participants have true referable DR in each trial arm and this figure will be the denominator in our primary outcome analysis.

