#### Primary outcome analysis: unadjusted analysis

The primary analysis will be a comparison of the proportion of persons with true referable DR out of all those with true referable DR (determined by the reference standard gradings) who attend the central ophthalmology clinic between the standard of care DR screening pathway (control) and the AI-supported DR screening pathway (intervention). The primary analysis of the primary outcome will be by logistic regression model using attendance at 8 weeks as the binary outcome, trial arm as the exposure and all participants who were classed as having referable DR by the reference standard measure will be included in the analysis. The intervention effect of AI-supported screening will be estimated as an OR with a 95% CI.

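### Recall of AI-missed cases can add attenders to the AI arm, so the statement that it does not affect the results is wrong for the primary outcome

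*Protocol article*

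**What the plan says.** All statements are in the protocol article.

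- **Interim analysis.** The safety review applies to this group: "Any images that are graded as referable DR by the Tanzanian graders but were graded as non-referable by the AI (potential false negatives". A senior grader looks at each such image. Where that review finds the referral threshold met, the participant is contacted and advised to come to the eye clinic. The section gives neither the mode nor the timing of that contact. It closes: "In such circumstances, the initial result from the AI grading will be used in the analysis and would therefore not affect the results".
- **Primary outcome measure.** The outcome, by arm, is this: "proportion of persons with true referable DR who attend the central ophthalmology clinic within 8 weeks of screening out of all those with true referable" (retinopathy). The UK-certified graders set the denominator: "It will be these gradings that will determine which participants have true referable DR in each trial arm".
- **Primary outcome analysis: unadjusted analysis.** A "logistic regression model using attendance at 8 weeks as the binary outcome, trial arm as the exposure", in which "all participants who were classed as having referable DR by the reference standard measure will be included in the analysis".
- **Follow-up assessment.** "All participants screened in the trial will be tracked to determine whether or not they attend the central ophthalmology clinic". The window is 8 weeks from screening.
- **Intervention arm.** The intervention has two components, AI grading and face-to-face counselling at the point of screening. Back-up grading by residents or a senior grader is not listed.

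**The concern.** Keeping the initial AI grade protects analyses that take the AI grade as an input, namely its sensitivity and specificity. The primary analysis has no such input. Whether a person is in the denominator depends on the UK grade, and whether they are in the numerator depends on a clinic visit. Retaining the AI grade changes neither, so it cannot cancel the effect of a recall that prompts a visit.

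The mechanism works in one arm only. In the standard arm a resident-positive participant is referred anyway. For an image there that the AI calls referable and the resident does not, no review is described. The AI arm therefore has a second chance at its missed cases and the standard arm has none. Missed cases are a real cost of the pathway described under Intervention arm, and the recall hides part of that cost in the primary comparison.

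**Working it through.** **1. Trace one participant.** Take an AI-arm participant with true referable DR whom the AI grades non-referable, the resident flags and the senior grader confirms.

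| Step | Rule | Result |
|---|---|---|
| Denominator | UK reference grade (Primary outcome measure) | Included |
| Tracking | Everyone screened (Follow-up assessment) | Attendance recorded |
| Arm | As randomised (Analysis plan) | AI arm |
| Numerator | Attends within 8 weeks | Counts if the visit is in time |
| AI grade | Not in the model | No effect |

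No section excludes or recodes such a visit, or holds the recall back beyond 8 weeks.

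**2. Is recall inside the window likely?** The Abstract says usual grading results typically come after 2–4 weeks, and Standard of care says results go by text or phone. Both statements concern the standard arm. If AI-arm images are graded on the same schedule, 8 − 4 = 4 to 8 − 2 = 6 weeks remain, less the time for senior review. Recall in time is likely but not documented.

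**3. Reproduce the plan's figure.** Sample size considerations gives 42% v 56%, 90% power and 266 true referable cases per arm. I take two-sided 5%, in line with the 95% CI. With pooled variance under the null and p̄ = 0.49:

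n = [1.960 √(2 × 0.49 × 0.51) + 1.282 √(0.42 × 0.58 + 0.56 × 0.44)]² / 0.14² = 265.9, so 266 per arm, with power 90.0%. Also 0.225 × 1182 = 265.95. The stated figure reproduces.

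**4. Size of the shift.** The AI sensitivity under AI system selection is 92.25%, from a validation study in Zambia.

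Expected AI misses = (1 − 0.9225) × 266 = 20.6.

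Added attendance = 0.0775 × r × c, where r is the share of misses flagged and confirmed and c is attendance in time after recall. Neither is given. I assume r = 50–90%, and c = 42%, borrowed from the programme's past follow-up rate among those referred.

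- r = 0.5: 0.0775 × 0.5 × 0.42 = 0.0163, or 1.6 points and 4.3 attenders.
- r = 0.9: 0.0775 × 0.9 × 0.42 = 0.0293, or 2.9 points and 7.8 attenders.

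Against the 14-point target this is 12% to 21%.

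**5. Effect on the test.** Suppose the arms would otherwise both be at 42%. With 266 per arm the standard error of the difference is about 4.3 points. Rejection probability is about Φ(δ/SE − 1.96) + Φ(−δ/SE − 1.96).

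| r | Shift | Pro-AI tail (nominal 2.5%) | Two-sided (nominal 5%) |
|---|---|---|---|
| 0.5 | 1.6 points | 5.7% | 6.7% |
| 0.9 | 2.9 points | 10.0% | 10.5% |

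Starting both arms at 0.9225 × 42% = 38.7% instead gives 6.7% and 10.6% two-sided.

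**6. If only half the recalls act in time.** The shift halves to 0.8–1.5 points, and two-sided rejection is 5.4–6.3% (5.4–6.4% from the 38.7% base).

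**7. Wider assumptions.** With r from 40% to 100% and c from 30% to 56%, the addition is 2.5 to 11.5 attenders, or 0.9 to 4.3 points.

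**The case against.** **The closing sentence may intend recalled participants to be scored by their AI result, as not referred.** It does not say so, and the primary outcome counts attendance, not referral. At best the sentence is unclear, and the attendance definitions do not support this reading. A separate analysis plan could hold a clear rule, but the claim as printed would still be wrong for the primary outcome.

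**The trial might be read as comparing AI plus human back-up with standard care.** Against that comparison the recall causes no bias. It is a legitimate target, but it is not the intervention the article describes.

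**A reader might infer that all AI misses are phoned back within 8 weeks and count as attenders.** The document does not support this. Recall applies only to misses that a resident flags and the senior grader confirms, and its mode and timing are not stated.

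**A reader might also fear a much larger bias from a lower AI sensitivity in this population.** The only sensitivity in the document is 92.25%. It comes from another country, and here ungradable images count as referable, so it may not carry over, but nothing in the article supports a particular lower value.

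**It might seem to follow that recalled attenders must be non-attenders in the primary analysis.** That departs from the stated outcome, and it counts as failures people who would have come anyway after the recall date. Which coding is primary is a choice of estimand. What is needed is that the choice be stated and the alternative shown.

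**Conclusion.** The no-effect statement is wrong for the primary outcome as defined. The direction is towards AI, relative to the pathway under Intervention arm. This rests on the definitions alone.

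The size is modest and much less certain: 4 to 8 extra attenders of 266 and roughly 7–11% two-sided rejection, conditional on the quoted sensitivity, the assumed 50–90% catch rate, 42% attendance after recall, and recall early enough to act within 8 weeks. The figures do not show that recall alone could produce the 14-point target effect. They do show a one-way shift that the article says does not exist.

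**What to change.** Leave the recall itself as it is; its timing and conduct are clinical matters and are not judged here. Change the analysis wording and the data capture:

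1. Delete the no-effect statement, or limit it to sensitivity and specificity.
2. Record the recall date for each recalled AI-arm participant and report the number recalled.
3. Before outcome data are seen, state how recall-prompted attendance counts in the primary outcome. If attendance is kept as observed, describe the comparison as AI with resident and senior back-up grading.
4. Pre-specify a sensitivity analysis in which AI-negative participants whose first attendance follows a recall are coded as non-attenders.
5. For time to presentation, and for the outcome whose denominator is everyone referred, state whether recalled participants count as referred.

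The cost is one date field, one extra analysis and a possibly less favourable AI-arm result. No additional participants are needed.

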### Patient and public involvement

Our previous research highlighted the importance of knowledge of the referral process and the fact that DR can be treated as key factors that impact referral adherence,^19^ both of which can be stated during point-of-screening counselling. We have held two FGDs with persons living with diabetes in the Kilimanjaro region, and who would be eligible for DR screening; the participants expressed a preference for a point-of-screening result over a delayed result.

